### Process evaluation

The process evaluation will collect quantitative data on recruitment and follow-up rates. In addition, qualitative data will be collected via a focus group with SSS advisors/managers delivering the intervention and through interviews with trial participants. This qualitative work will identify barriers and facilitators to trial recruitment and adherence and explore the acceptability of study processes and procedures. Full details of the process evaluation are reported in Additional file 1.

### Baseline measures

In a baseline questionnaire, administered by the SSS advisor before randomisation, we will assess measures which have been shown to predict postpartum smoking relapse [29] and which we would want to ensure are similar for the three study groups, as potential confounders of any effects on smoking cessation (see Table 1). These measures are:
AgeEthnicityHighest educational qualificationOccupationGestationLevel of cigarette consumption before pregnancyExpired CO level in ppmParity (i.e. number of previous pregnancies that have gone beyond 24 weeks)Assessment of any smoking in the home and of whether partner smokesLength of time since last smoking (months/weeks)Self-efficacy: rating of ‘How confident are you that you will continue not to smoke at least until your baby’s first birthday?’ (not at all confident, slightly confident, moderately confident, very confident, extremely confident) [30]Depression: Edinburgh Postnatal Depression Scale [31] (for the item **‘The thought of harming myself has occurred to me**’**, if women respond ‘Yes, quite often’ or ‘sometimes’, they will be referred to** their health visitor, family nurse partnership or GP)Breastfeeding intent [32]Alcohol consumption: Alcohol Use Disorders Identification-Consumption (AUDIT-C) test [33, 34]Use of support for smoking cessation beyond what is provided in the trialWhether they recruited a significant other supporter (SOS) during their pregnancyUse of nicotine replacement therapy (NRT) in the last week and main types of NRT usedUse of heat-not-burn products in the last weekUse of e-cigarettes in the last week

### Participant timeline {13}

The trial flow diagram is presented in Fig. 1.

**Fig. 1 Fig1:**
[figure not shown]
Trial flow diagram

#### Sample size {14}

We estimate that the proposed sample size of 900 women will give 90% power at an alpha threshold of 0.017 to detect a difference in abstinence rates across any two groups of 13.6% at 12-month follow-up. It is anticipated that the abstinence rate in the control group will be 9% at 12-month follow-up, that there will be 22.6% abstinence at 12 months follow-up in the 3-month incentives group and 36.2% abstinence at 12 months follow-up in the 12 months incentives group. The figure of 9% in the no incentives group is conservatively based on the assumption that over 90% of women without incentives may relapse by 12 months postpartum [3]. The estimate of 13.6% difference is based on the group difference found by Tappin and colleagues in a study of incentives during pregnancy [34]. The threshold for alpha is reduced to 0.017 to correct for multiplicity and allow comparisons across the three arms. This sample size will also give 100% power to detect a linear trend in abstinence across the three groups (*p* < 0.05) from control to 12-month intervention.

#### Recruitment {15}

At the time that women join the Smokefree Pregnancy programme, which is most commonly following their first antenatal booking visit at 8–12 weeks gestation, they will be informed by their stop smoking service (SSS) advisor that those who are confirmed as abstinent from smoking at around 36 weeks gestation (acceptable range, 34 weeks gestation to 2 weeks postpartum) will be offered the opportunity to join a research study in which they may or may not be offered shopping vouchers to remain abstinent through 12 months postpartum.

Women confirmed as abstinent (CO < 4 ppm) by their SSS at around 32 weeks gestation will be given or sent a ‘generic’ PIS about the study. We decided to first provide a generic PIS, explaining that incentives may or may not be offered, but not giving the specific details of the three study groups, in order to reduce potential dissatisfaction and dropout if women are not offered the highest value of incentives. It will be explained that if they are still confirmed as abstinent at their 36-week appointment, and meet other eligibility criteria, they will have the opportunity to discuss the study and decide if they want to join. All women confirmed as abstinent at around 36 weeks gestation by their SSS (acceptable range, 34 weeks gestation to 2 weeks postpartum), and meeting other eligibility criteria, will be invited by their SSS advisor to join the study. If women give birth before their 36 week appointment they will still be eligible as long they join the study within 2 weeks of the birth of the baby and meet other eligibility criteria. The SSS advisor will explain that we are running an RCT examining the effects of offering shopping vouchers on women’s smoking cessation during the 12 months after their baby is born and seek consent to participate. See {26a} for a description of the consent process.

A screening form will be completed by the SSS advisor to record number of women approached, eligibility, number of women declining to take part or not eligible, and reasons for being ineligible or declining, if women are willing to provide this information.

If a face-to-face visit and/or multiple use CO test is not possible (e.g. in order to maintain social distancing) the CO reading to determine eligibility will be taken by a single-person, self-administered CO monitor, posted to the woman following her appointment at 32 week’s gestation, and used by the woman at home (iCO^TM^ Smokerlyzer, Bedfont Scientific Ltd.) [28]. The CO reading will be transferred to the SSS advisor using an app. Women who do not have a device (e.g. phone) that is compatible with this app will not be eligible to join the trial. The baseline questionnaire will be administered by the stop smoking advisor over the phone. When the COVID-19 restrictions have been lifted, we will give participants the option of continuing with the above approach or they can choose to have face-to-face appointments.

Details of those consenting to participate in the trial will be entered by the SSS advisor on to a secure University of Stirling online server which will generate a randomisation code. Some participants may be disappointed not to be allocated to one of the incentives groups and the SSS advisors will be trained to respond appropriately to this. Following randomisation, the participant’s screening form, baseline questionnaire and consent form will be sent to the study principal investigator who will review this documentation and confirm eligibility.

The patient’s clinical care team (e.g. midwife, health visitor, GP) will already have been made aware that the woman is taking part in the Greater Manchester Smokefree Pregnancy programme; therefore, we will not be sending a separate letter to patient’s general physicians (GPs) when they join the trial.

#### Concealment mechanism {16b}

Randomisation will use a web-based randomisation system.

### Implementation {16c}

SSS advisors at each site will enrol participants and request the group allocation.

### Assignment of interventions: blinding

#### Who will be blinded {17a}

Due to the nature of the intervention, participants and the SSS advisors delivering the intervention will not be blinded to the treatment received. Nor will SSS advisors or researchers who ascertain smoking status at 3 and 12 months postpartum be blinded; however, there is low risk of bias as smoking status is biochemically validated. Those involved in the data analyses will be blinded to the group allocation.

#### Procedure for unblinding if needed {17b}

Participants and SSS staff delivering the intervention are not blinded.

### Data collection and management

#### Plans for assessment and collection of outcomes {18a}

Data will be collected via questionnaires at baseline and at three and 12 months postpartum. Questionnaires will be either self-completed by participants or, during COVID-19 restrictions, will be administered by SSS advisors over the telephone. Demographic information will be collected at baseline via questionnaire. CO readings will be collected at baseline and at 3 and 12 months postpartum during a face-to-face visit or, during COVID-19 restrictions, remotely via an app. For those who report smoking abstinence at 12 months postpartum saliva, for cotinine/anabasine testing, will be collected face-to-face or, during COVID-19 restrictions, saliva collection kits will be posted to participants and participants will post the saliva sample to the laboratory.

#### Plans to promote participant retention and complete follow-up {18b}

In order to maximise the number of participants who complete follow-ups, especially among those in the control group and those who have relapsed to smoking, all participants will be offered a £20 voucher payment, for completing a follow-up assessment at both 3 months and 12 months postpartum (i.e. £20 for each assessment). The assessment includes completion of a questionnaire and biochemical assessment of smoking status. A previous UK trial of incentives for smoking cessation in pregnancy showed that such a payment motivates women to attend follow-ups [29]. Telephone contact for follow-up will be attempted on up to five occasions. If a participant has been asked to post a saliva sample to the laboratory and the saliva sample has not arrived, the participant will be contacted and reminded to send the sample.

#### Data management {19}

All trial participants are given an individual trial number which will be used on all case report forms (CRF) for that participant. Researchers at the University of Stirling will enter data from CRFs into the secure trial database. To check for systematic errors, double data entry will be conducted for a random selection of 10% of CRFs. University of Stirling researchers will review CRFs and the database for range errors and for missing data.

#### Confidentiality {27}

All collected information will be kept strictly confidential and will be stored in accordance with the General Data Protection Regulation (GDPR) and the latest Directive on Good Clinical Practice (GCP). Confidentiality of patient’s personal data is ensured by not collecting patient names on CRFs and limiting access to personal information held on the databases. At trial enrolment, the participant will be issued a participant identification number and this will be the primary identifier for the participant, with secondary identifiers of month and year of birth and initials. Any paper copies of personal trial data will be kept at the participating site in a secure location with restricted access. Following consent, identifiable data will be kept in a secure database at each site and at the University of Stirling, to allow authorised members of the site team to contact participants in order to arrange appointments/assessments.

Any paper copies of consent form, with patient name and signature, will be kept securely at the trial site with a copy sent to the University of Stirling for monitoring purposes. Consent forms will not be kept with any additional patient data.

### Plans for collection, laboratory evaluation and storage of biological specimens for genetic or molecular analysis in this trial/future use {33}

None

### Statistical methods

#### Statistical methods for primary and secondary outcomes {20a}

The plan for statistical analysis is reported here in accordance with guidance for RCTS [35, 36].

We will use descriptive statistics to present the baseline characteristics of the three study groups. Descriptive statistics will also be used to report rates of recruitment, retention and follow-up at 3 months and 12 months postpartum and to report the numbers of women who relapsed before the birth vs after the birth, separately for the two study groups. Again, descriptive statistics will be used to present the following secondary outcomes at 3 and 12 months postpartum: use of nicotine products, smoking in the home, partner smoking status, use of additional smoking cessation support beyond that provided in the trial and use of the iCO (single-person use) monitor beyond that required for the research.

Analyses of smoking status, for primary and secondary outcomes, will be performed for the intention-to-treat population and reported in accordance with the Consolidated Standards of Reporting Trials (CONSORT) statement [37, 38], including all women who are randomised and meet the eligibility criteria. If ineligible persons are mistakenly randomised into the trial, the independent trial steering committee will review the case for removing the participant from the analysis, such that this decision is unbiased and not influenced by events that occurred after randomisation (and may therefore be affected by whether patients received experimental or control treatment) [39].

Women lost to follow-up will be presumed to have returned to smoking [19]. This assumption is standard in the smoking cessation literature as the pattern of missingness is not random. We will compare differences in smoking cessation outcomes between all three treatment groups, using logistic regression adjusted for the random effect of site (i.e. NHS Trust), with statistical significance determined by the likelihood-ratio test, and with pairwise comparisons between treatment groups in accordance with the study objectives, using a *p* value of 0.017 adjusted for the three comparisons. The estimate of effect will be given as the odds ratio and 95% confidence interval for each of the three comparisons. We will also look for a linear trend in smoking cessation across the three groups, by examining the significance (*p* < 0.05) of a linear contrast across the groups from control to 12-month intervention.

All outcomes will be analysed collectively following the completion of the final follow-up at 12 months postpartum. A more detailed statistical analysis plan will be agreed to before the end of data entry and before the treatment code is broken.

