### Trial status

The FIPPS trial is currently recruiting in four UK centres/Hospital Trusts in Greater Manchester. Recruitment began in February 2019 and is due to end In August 2021, with follow-up completed by September 2022. The trial has a TSC which has convened five times. During COVID-19, due to a combination of lack face-to-face screening of women’s smoking status in pregnancy and reduced staffing due to illness or ‘shielding’, fewer women have joined the pregnancy cessation scheme than expected and therefore there has been a smaller pool of women to screen to join the trial. Thus, the trial is behind target and will not recruit the target of 900 women by August 2021. As of June 30th, 2021, 424 participants have been recruited. Based on recent recruitment rates, we anticipate recruiting approximately 462 women by the end of August 2021. We do not have the resources to continue recruiting past this date. This has implications for the power calculations. Assuming *N* = 154 in each of the three study groups and effect sizes as estimated in the original sample size calculation, then the power for the three comparisons, all with an alpha threshold of 0.017, will be:

60% power for 3-month incentives versus 12-month incentive group comparison

82% power for the no incentives versus 3-month incentive group comparison

100% power for the no incentives versus 12-month incentive group comparison

The power for examining the significance (*p* < 0.05) of a linear contrast across the three groups from control to 12-month intervention will be 100%.

This article is based on protocol version V7.0, 16th November 2020. For the registered trial protocol and updates see 10.1186/ISRCTN55218215

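### The flat 0.017 threshold for the three pairwise comparisons is valid but needlessly conservative; a three-group step-down test would raise power for 12 v 3 months from 60% to about 75% at the planned rates.

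*Protocol article*

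**What the plan says.** Sample size {14} gives the reason for the level: "The threshold for alpha is reduced to 0.017 to correct for multiplicity and allow comparisons across the three arms". It plans that "the abstinence rate in the control group will be 9% at 12-month follow-up", with "22.6% abstinence at 12 months follow-up in the 3-month incentives group" and "36.2% abstinence at 12 months follow-up in the 12 months incentives group", and says that the "proposed sample size of 900 women will give 90% power at an alpha threshold of 0.017" for a difference of 13.6 percentage points between any two groups.

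Statistical methods {20a} carries the level into the analysis. It opens with an overall comparison ("We will compare differences in smoking cessation outcomes between all three treatment groups") by logistic regression and the likelihood-ratio test, then makes the pairwise comparisons at a p "value of 0.017 adjusted for the three comparisons". No level is given for the overall test, and it is not described as a condition for the pairwise tests. Effects are to be reported with 95% confidence intervals, and a linear trend is tested separately at 0.05.

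Trial status reports that recruitment will end at about 462 women, 154 per group, with no resources to go further. At 0.017 this leaves "60% power for 3-month incentives versus 12-month incentive group comparison", 82% for 3 months v none and 100% for 12 months v none. The statistical methods section adds that a more detailed analysis plan will be agreed before the treatment code is broken.

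**The concern.** A flat 0.017 protects against all three pairwise nulls being true at once, and keeps that protection after one of them has been rejected. With three groups this is more than is needed. If any two groups differ, the third cannot equal both, so at most one of the other two nulls can be true, and no further correction is needed between those two tests.

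The comparison that loses most is 12 v 3 months. It is hypothesis (iii) and bears on whether the £300 schedule achieves more than the £120 one. It has the lowest stated power, and the article rules out further recruitment, so the choice of testing procedure is one of the few ways left to improve it.

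**Working it through.** **Inputs.** Planned abstinence 9%, 22.6% and 36.2%, with 300 per arm (900/3), from Sample size {14}. Revised size of 154 per arm, from Trial status. Level 0.017, from Statistical methods {20a}. Women lost to follow-up count as smoking, so no allowance for dropout is needed. Sidedness is not stated; two-sided is assumed, and it reproduces the article's figures.

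**Formula.** Pooled normal approximation: power = Φ[(d − z·s0)/s1], where d is the difference in rates, s0 = √(2p̄(1−p̄)/n), s1 = √((p1(1−p1)+p2(1−p2))/n), and z = 2.387 at 0.017 or 1.960 at 0.05.

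**Step 1: reproduce the article.**
- 300 per arm, 22.6 v 36.2%: 90.0% (stated 90%).
- 154 per arm, 22.6 v 36.2%: d = 0.136, s0 = 0.0519, s1 = 0.0513; Φ[(0.136 − 2.387×0.0519)/0.0513] = 59.3% (stated 60%).
- 154 per arm, 9 v 22.6%: s0 = 0.0416, s1 = 0.0408; 81.6% (stated 82%).
- 154 per arm, 9 v 36.2%: 99.98% (stated 100%).

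**Step 2: same formula at 0.05, the level that applies after a first rejection.**
- 22.6 v 36.2%: Φ[(0.136 − 1.960×0.0519)/0.0513] = 74.8%.
- 9 v 22.6%: 90.9%.
- 9 v 36.2%: about 100%.

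**Step 3: include the first step.** The formula at 0.05 ignores the need for one rejection at 0.0167. Simulating binomial outcomes at 154 per arm with pooled two-proportion tests (300,000 to 400,000 trials per scenario) gives:

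| Planned rates 9/22.6/36.2% | Flat 0.017 | Step-down |
|---|---|---|
| 12 v 3 months | 60% | 75% |
| 3 months v none | 83% | 92% |
| 12 months v none | about 100% | about 100% |
| All three significant | 45% | 67% |

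The first step costs almost nothing here, because 12 months v none is nearly always rejected. For 3 months v none, 91% is the figure on the same formula basis as the stated 82%; the simulated 92% pairs with 83%.

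**Step 4: family-wise error of the step-down over the three pairwise tests.** With pooled tests: 4.5% at 20/20/20%, 4.9% at 9/9/36%, 5.0% at 9/36/36% and 4.1% at 9/9/16%. With likelihood-ratio tests, as the article plans, it reaches 5.3% when two of the groups are equal at 9%. A single unadjusted likelihood-ratio test shows the same 5.3%, so the excess comes from the large-sample approximation and not from the step-down.

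**Step 5: the price.** With 3- and 12-month incentives truly equal (9/22.6/22.6%), the chance of declaring them different is 1.7% under flat 0.017 and 5.0% under the step-down.

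**Step 6: other rates (assumed, to show the range), 12 v 3 months at 154 per arm.**
- 9/19/29%: 37% to 54%.
- 9/16/23%: 20% to 34%.

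**The case against.** The strongest reply is that nothing in the article is wrong. Sample size, analysis and trial status all use the same 0.017, the correction is valid, the power figures reproduce and the shortfall is disclosed. That stands. A reader might infer that the multiplicity adjustment is mistaken or the stated power misleading; the documents support neither. The later analysis plan is also a natural place for a step-down rule. But the article does not leave the matter open: it fixes a flat 0.017 and quotes its power on that basis.

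Four further limits stand.
- **The gain is not free.** The false-positive rate for a truly null pair rises about threefold once another pair clearly differs, and this includes 12 v 3 months. It stays within the nominal 5%.
- **75% is not a general result.** It needs the planned steps between arms. With smaller steps the comparison stays poorly powered under either rule.
- **The 5% covers only the three pairwise tests.** A reader might take it as the error rate for all four primary hypotheses. The linear trend is tested at 0.05 outside the family, now and after the change. For equally spaced arms its contrast is essentially 12 months v none, and any rejection among the four tests under a global null has a probability of about 7 to 8% under both rules.
- **The planned overall test is not the same procedure.** Gating pairwise tests at 0.05 on the three-group likelihood-ratio test is a valid closed test, but it rests on a different first step. The two rules disagreed in about 1% of simulated null trials and in 2 to 4% with smaller effects.

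**Conclusion.** The concern holds as a point of efficiency. With exactly three groups, and apart from the rounding of 0.0167 to 0.017, the step-down rejects everything that the flat rule rejects, and sometimes more, at the same nominal 5% for the pairwise family. At 154 per arm and the planned rates the chance of missing a true difference between 12 and 3 months falls from about 40% to about 25%, with no more participants.

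The figures assume two-sided tests, 154 per arm and no site effect. The planned model has a random effect for Trust; with four Trusts and randomisation stratified by Trust, this is assumed to change little. The improvement is worth making because it is cheap and still open, not because the present rule is unsound.

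**What to change.** Before the treatment code is broken, replace the flat threshold in Statistical methods {20a}, and in the analysis plan, with a rule such as: order the three pairwise p values; test the smallest at 0.0167; if it is significant, test each of the other two at 0.05; otherwise stop. The alternative is to make the three-group likelihood-ratio test at 0.05 an explicit gate and test each pair at 0.05 only if it is passed. Choose one and name it. State that the 5% covers the three pairwise tests and that the linear trend stands outside.

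Restate the Trial status power as about 75% (12 v 3 months), 91% (3 months v none) and 100% (12 months v none), with the range under smaller differences.

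The cost is a sentence or two in each document, the higher false-positive rate for a null pair described above, and the loss of any single confidence level that matches the decisions. The last is a small loss, since the planned 95% intervals already do not match a 0.017 threshold.

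### The three pairwise odds ratios are tested at p<0.017 but reported with unlabelled, unadjusted 95% intervals, so an interval can exclude 1 when the pre-specified test is not met

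*Protocol article*

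**What the plan says.** The section Statistical methods for primary and secondary outcomes {20a} compares abstinence between the groups by logistic regression with a random effect of site, "with statistical significance determined by the likelihood-ratio test". The pairwise comparisons use a p "value of 0.017 adjusted for the three comparisons". The next sentence turns to estimation: "The estimate of effect will be given as the odds ratio and 95% confidence interval for each of the three comparisons".

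Sample size {14} gives the reason for the lower threshold: "The threshold for alpha is reduced to 0.017 to correct for multiplicity and allow comparisons across the three arms". Trial status repeats 0.017 when it restates power for the smaller trial now expected, with 154 women per group.

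The article does not say that the 95% intervals are unadjusted or descriptive, and it plans no interval at the level of the test.

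**The concern.** Tests and intervals for the same three comparisons are set at different error levels, without comment. The tests carry a correction for three comparisons and the intervals do not. A result with p between 0.017 and 0.05 would appear as an odds ratio whose interval lies wholly on one side of 1, beside a test that the plan counts as not met.

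The comparison most exposed is 12-month against 3-month incentives, which is hypothesis (iii). It decides whether the scheme worth up to £300 does better than the one worth up to £120, and Trial status gives it only 60% power. The Discussion says the results are meant to inform national guidance. A reader who goes by the interval could credit the longer scheme with a benefit that the plan's own rule does not declare.

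**Working it through.** **Inputs.** From {20a}: threshold 0.017 and interval level 95%. From Sample size {14}: "the abstinence rate in the control group will be 9% at 12-month follow-up", "22.6% abstinence at 12 months follow-up in the 3-month incentives group", "36.2% abstinence at 12 months follow-up in the 12 months incentives group", and 900 women, which is 300 per arm at 1:1:1. From Trial status: 154 per arm. Assumptions: two-sided tests, pairwise p values from the likelihood-ratio test, site ignored.

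**1. The plan's own figures.** 0.05/3 = 0.0167, which rounds to 0.017. For the limiting pair, 22.6% against 36.2%, the mean rate is 0.294. With the pooled-variance formula

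power = Φ{[|p₂−p₁| − z·√(2p̄(1−p̄)/n)] / √[(p₁(1−p₁)+p₂(1−p₂))/n]}, z = 2.387:

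- n = 300: (0.136 − 2.387×0.03720)/0.03678 = 1.283, so power is 90.0%. The article states 90%.
- n = 154: (0.136 − 2.387×0.05192)/0.05134 = 0.235, so power is 59.3%. The article states 60%.
- n = 154, 9% against 22.6%: 81.6%. The article states 82%.
- n = 154, 9% against 36.2%: 99.98%. The article states 100%.

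Sample size, power and threshold reproduce. None of them is in question.

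**2. The interval that matches the test.** 1 − 0.017 = 0.983, a 98.3% interval. Its multiplier is 2.387 against 1.960 for 95%, and 2.387/1.960 = 1.218, so it is about 22% wider on the log-odds scale.

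**3. One discordant result.** Take 14/154 (9.1%) against 27/154 (17.5%).

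- Odds ratio = (27/127)/(14/140) = 2.13; log odds ratio 0.754.
- Standard error = √(1/14 + 1/140 + 1/27 + 1/127) = 0.351.
- 95% interval: exp(0.754 ± 1.960×0.351) = 1.07 to 4.23, which excludes 1.
- Likelihood-ratio p = 0.028, which does not meet 0.017.
- 98.3% interval: exp(0.754 ± 2.387×0.351) = 0.92 to 4.92, which includes 1 and agrees with the test.

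**4. How often this happens.** P(0.017≤p<0.05), summed over all pairs of binomial outcomes, at the planned rates:

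| Comparison | 154 per arm | 300 per arm |
|---|---|---|
| 12-month v 3-month | 15.5% | 5.6% |
| 3-month v control | 8.5% | 0.8% |
| 12-month v control | 0.01% | about 0% |

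With no true difference it is about 0.05 − 0.017 = 3.3% per comparison. A normal approximation on the log odds ratio at 154 per arm gives 15.4%, 10.3% and 0.1%. The exact sums are used above.

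**5. Joint coverage.** Three equal groups were simulated under a normal model. All three pairwise intervals cover their true values together in about 87.8% of trials at 1.960 and about 95.5% at 2.387.

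**The case against.** The decision rule is clear. The likelihood-ratio test at 0.017 settles significance, and the interval comes in a separate sentence about the estimate of effect, which gives it no role in the decision. Unadjusted 95% intervals beside a Bonferroni threshold are common and legitimate. A reader who has the p value and the threshold can resolve a discordant case. The article also promises a more detailed statistical analysis plan before the treatment code is broken, and that plan could add a label without reversing anything.

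Most of this stands, and it limits the point. A reader might infer that the plan contradicts itself, that its error rate is inflated, or that the intervals are simply too narrow. The document supports none of these. The 0.017 tests control type I error whatever interval is printed. Each 95% interval has its nominal coverage for its own odds ratio, and the article claims no joint coverage. Nor is the conflict likely everywhere: it is negligible for 12-month against control, and for 3-month against control at the planned 300 per arm it is under 1%.

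Two things remain. The article itself fixes the 95% level for these comparisons, so this is not merely a detail left open. And it attaches no label to the intervals, although the sentence before has just corrected the same comparisons for multiplicity.

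**Conclusion.** The point holds as a mismatch in reporting, of minor to moderate severity. If the article is followed as written, it can publish an interval that excludes 1 beside a test that is not met. At the planned rates and 154 per arm, that happens in about one trial in six or seven for 12-month against 3-month incentives (15.5%) and about one in twelve for 3-month against control (8.5%). The recruitment shortfall nearly triples the first figure: 15.5/5.6 = 2.8. Jointly the three intervals cover about 88%, against about 95.5% for intervals matched to the test.

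These frequencies rest on the article's assumed abstinence rates, two-sided tests and no allowance for site. Other true rates would change them. That the mismatch exists does not depend on these assumptions. Close to the boundary a Wald interval and a likelihood-ratio test can differ slightly, which does not alter the conclusion.

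**What to change.** In {20a}, or in the detailed analysis plan before the treatment code is broken:

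- report 98.3% confidence intervals for the three pairwise odds ratios, as those that match the 0.017 test;
- keep the 95% intervals beside them, labelled as unadjusted for multiplicity;
- state that significance of the pairwise comparisons is judged only at p<0.017.

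This is a change of a line or two. Sample size, power, threshold and point estimates stay as they are. The cost is that the matching intervals are about 22% wider on the log-odds scale and that two intervals are reported for each comparison.
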